## 1. Introduction.

Current treatment of cutaneous leishmaniasis is inadequate, toxic, costly, requires repeated injections, and is not effective in all cases. Pentavalent antimonials were developed over a half century ago, and are administered by repeated injection for 20 consecutive days. They are expensive and toxic (fatigue, cardiopathy, pancreatitis), yet they remain the mainstay of anti-*Leishmania* therapy in the developing world. New paradigms to treat this chronic infection are needed. .

Strong rationale for this proposal emanates from the integration of distinct and important recent developments. First, a relatively new immunomodulating macrophage activating compound, termed imiquimod (AldaraTM) has been developed by 3M Pharmaceuticals and has regulatory approval in the US, Canada, and the European Union for the treatment of skin infections with human papillomaviruses (HPV). As a topical agent, imiquimod has been shown to be safe and effective against HPV infections. Therefore the cost of development has already been incurred. Second, we have shown that imiquimod can activate macrophage killing of *Leishmania in vitro* and in mouse model experiments. Third, we have completed phase I clinical trials in Peru showing that, in cutaneous leishmaniasis patients which have not responded to treatment with a standard course of pentavalent antimony (Glucantime), the combination of imiquimod with standard pentavalent antimony therapy was safe and significantly increased the rate of cure with *L. (V) braziliensis* and *L. (V) peruviana* infections (Clin. Infect. Dis. 33: 1847-1851, 2001; Clin. Infect. Dis. 40: 1395-1403, 2005). These developments provide a foundation to establish whether cutaneous leishmaniasis patients in Peru who have not previously been treated with pentavalent antimony can be treated with a combination of pentavalent antimony (GlucantimeTM) and imiquimod (AldaraTM). This study will be conducted in accordance with ICH harmonised tripartite guidelines for good clinical practice.

## 2. Trial Objective:

The objective is to determine whether patients who have not previously been treated with pentavalent antimony can be more effectively treated with a combination of pentavalent antimony and imiquimod than with pentavalent antimony alone.

This study will test whether addition of imiquimod to standard antimony therapy provides a significant benefit in subjects with newly diagnosed disease. Based on our previous results, we hypothesize that lesions in patients who receive the combined treatment of pentavalent antimony and imiquimod as a first line therapy will resolve more rapidly and produce less scarring than treatment with pentavalent antimony alone. This is a relevant question since our previous studies involved only patients with cutaneous leishmaniasis who had previously failed one course of pentavalent antimony therapy (Clin. Infect. Dis. 33: 1847, 2001; Clin. Infect. Dis. 40: 1395, 2005).

## 3. Trial Design

A randomized, double-blind clinical trial will involve a total of 80 patients. The randomization procedure is detailed below in section 6 under Randomization, blinding and assignment of treatment. The trial will be conducted at the Instituto de Medicina Tropical Alexander von Humbolt -Universidad Peruana Cayetano Heredia (IMTA vH-UPCH) in Lima site for patients infected with *L. peruviana* and the IMTA vH-UPCH Cusco site, for patients infected with *L. braziliensis*. The groups will be assigned the following regimens: The Lima arm will include 20 experimental and 20 placebo patients. Likewise, the Cusco arm will include 20 experimental and 20 placebo patients.

Control: Standard dose of pentavalent antimony (Glucantime™ 20 mg/kg IV infusion/day for 20 days) plus placebo cream (thin layer cream applied to each lesion three times per week for 20 days).

Experimental: Standard dose of pentavalent antimony (Glucantime™ 20 mg/kg IV infusion/day for 20 days) plus standard dose of Aldara™ (5% imiquimod cream applied

to each lesion three times per week for 20 days). All patients will be subjected to follow-up clinical evaluations at 1, 2, 3, 6, 9 and 12 months after the last treatment (Day 20). The follow up evaluations will be performed by the investigation team. The endpoint for clinical cure will be complete re-epithelialization of the lesion with no sign of inflammation.

Patients will be recruited from highly endemic areas which are within one day driving from the study centers in Lima and Cusco including Ancash, Churin, Yumpe, , Sicuani, and surrounding areas. Note, that patients treated in Cusco have predominantly *L. braziliensis* infections and patients treated in Lima, Ancash, Churin and Yumpe have predominantly *L. peruviana* infections. Study teams (consisting of a UPCH trained doctors, nurses, and technicians) will carry out the treatments at IMTAvH Lima site under the supervision of [name] and at IMTAvH Cusco site under the supervision of [name]. [name] will oversee the treatments and follow-up at each center. Following the completion of therapy, the teams will then coordinate follow-up visits at 1, 2, 3, 6, 9 and 12 months. [name] will coordinate the follow up visits as he has done previously in these types of studies.

#### Personnel Responsibilities in Peru

Two research units will be established to work out at the IMTAvH –UPCH Lima and Cusco sites. This will ensure sufficient patients are recruited at each site and also determine whether the treatments work similarly for *L. braziliensis* (Cusco site) and *L. peruviana* (Lima site). All personnel will have been trained by [name] at UPCH.

#### **Lima Site**

This will be the study coordination site where the Peruvian Principal Investigator [name] will be based and from where the project will be managed. He will be supported by an administrative assistant, an accountant and the study pharmacist. The Lima site study team consists of an MD, study nurse, laboratory technician and field

worker who will recruit and care for the patients during the study and carry out all study procedures. The Lima site will be the place for the study coordinator, who will work together with [name].

### **Cusco Site**

A team consisting of 2 MDs, study nurse and field worker will staff this trial site and will be supported by the Lima group

Samples will be sent to UPOCH in Lima to for PCR analysis, culturing of parasites and storage.

## **4. Eligibility Criteria**

### **4.1 Inclusion Criteria**

Patients must meet ALL of the following criteria to be eligible for inclusion into the study.

- a) Males and females between the ages of 5 and 65 years
- b) Confirmed diagnosis of cutaneous leishmaniasis (CL) defined as:
  - \* Presence of an active ulcerative cutaneous *Leishmania* lesion, and
  - \* Positive identification of parasite from lesion smear (e.g.: microscopy, culture, or PCR)
- c) Time of disease more than 4 weeks.
- d) No prior therapy for CL with anti-leishmanial agents.
- e) Female patients of childbearing potential must have a negative urine pregnancy test at screening, must not be breast-feeding and are required to use adequate contraception during the 20 days of the treatment.
- f) Must give informed written consent or have a parent provide consent for anyone under the age of 18. The patient must be willing to participate in all treatment evaluation visits, be reachable by telephone or accessible to personal contact by the study site personnel.

- g) Stability of residence or be reachable by the study personal.

#### 4.2 Exclusion Criteria

Patients must have NONE of the following criteria to be eligible for inclusion into the study:

- a) Having a lesion(s)  $> 25 \text{ cm}^2$
- b) More than 6 cutaneous lesions.
- c) Have a mucosal lesion.
- d) History of previous exposure to imiquimod or anti-*Leishmania* treatment.
- d) Participation in another experimental protocol and/or have received investigational products within 30 days prior to study entry.
- e) History of any acute or chronic illness (other than CL) or medication that, in the opinion of the investigators, may interfere with the evaluation of the trial (i.e History of heart illness, corticotherapy)
- f) History of significant psychiatric illness.
- g) History of previous anaphylaxis or severe allergic reaction to one or more of the proposed drugs.
- h) Patients who are unlikely to cooperate with the requirements of the study protocol.
- i) Concomitant infection (ex. Bartonellosis, Sporotrichosis, Mycobacteria)
- j) Women who are pregnant or breast feeding.

..

These inclusion and exclusion criteria were established in order to provide the optimal opportunity for treatment response.

## 5. Screening Evaluations

Screening evaluations will occur within the 30-day period prior to Day 1 (i.e. Day – 30 to Day 0). The purpose of the screening period is to ensure that the patients meet

all eligibility criteria and that they entirely comprehend the protocol and its requirements before signing the consent form and agreeing to enter the trial.

The screening procedure includes the following assessments as listed below and recorded on the **clinical report form (CRF)** for the study:

- a) Provision of study informed consents and patient signature of these informed consent documents.
- b) Positive diagnosis of CL by smear or PCR. PCR will be used to verify whether the patient is infected with *L. braziliensis* or *L. peruviana*
- c) Urine pregnancy test for any female patients of childbearing potential. Test result must be negative in order to proceed.
- d) Documentation of medical history.
- e) Record of any concomitant medications.
- f) Assessment of vital signs.
- g) Perform a complete physical exam. The location, size and description of the active cutaneous lesions must be noted. Every mucosal membrane will be examined and record the presence or absence of any mucosal lesion.
- h) Record any other disease symptoms the patient may experience.
- i) Electrocardiogram: Will be performed prior to treatment
- j) Collect blood as follows:  
Approximately 2.5 ml anticoagulated (EDTA) whole blood for CBC, white cell differential and platelet count.
- k) Approximately 8.5 ml whole blood into serum separator tube (SST) for serum chemistry and serology testing for chemistries to include: ALT, AST, total bilirubin, alkaline phosphatase, pancreatic amylase, glucose and creatinine.
- l) Obtain skin biopsy for diagnostic procedures (except for lesions from the face).

## **6. Randomization, blinding and assignment of treatment.**

A randomization list from 1-80 will be generated by [name] at McGill University using a ratio of 1:1 to either the pentavalent antimony plus imiquimod arm or the pentavalent antimony plus placebo arm. The list will then be provided to a pharmacist, [name] at UPOCH who will be responsible for therapy preparation. This individual will not be involved in conducting the trials and therefore cannot administer the treatment or conduct patient evaluation(s). This list will contain the study I.D. numbers (1-80) and corresponding treatment assignments and remain completely blinded to the study investigators who will be treating and evaluating the patients.

Each patient will be assigned by the study doctor a study I.D. number from the above randomized list assigned in sequential order when he/she is enrolled in the trial. The study doctor at each site will ask to the study coordinator for the study ID number. The study ID number will be provide to the study coordinator by the pharmacist. This study ID number will be entered on the CRF for that patient. The nurse will then administer the treatment as detailed in section 7. The study doctor will carry out the evaluation and the nurse, doctor, and technician will remain blinded for the treatment and evaluation period.

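### Section 6 draws both sites' patients from one sequential 1:1 list, which does not ensure the 20 imiquimod and 20 placebo per site that Section 3 states.

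*Protocol*

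**What the plan says.** Section 3 of the protocol gives the size, "A randomized, double-blind clinical trial will involve a total of 80 patients", and then the composition of each site: "The Lima arm will include 20 experimental and 20 placebo patients" and "Likewise, the Cusco arm will include 20 experimental and 20 placebo patients". It assigns *L. peruviana* patients to Lima and *L. braziliensis* patients to Cusco, adding that each place has predominantly that species. Under Personnel Responsibilities in Peru, one reason given for having two sites is to "determine whether the treatments work similarly for" the two species.

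Section 6 sets the allocation procedure. A statistician prepares one list, "using a ratio of 1:1 to either the pentavalent antimony plus imiquimod arm" or the placebo arm. On its content: "This list will contain the study I.D. numbers (1-80) and corresponding treatment assignments". On its use: "Each patient will be assigned by the study doctor a study I.D. number from the above randomized list assigned in sequential order". Both sites draw from it by the same route: "The study doctor at each site will ask to the study coordinator for the study ID number", and the coordinator obtains that number from the pharmacist. Section 13 (Treatment preparation) refers to the same list and says that packages carry only the study ID. Neither section mentions site strata, separate lists, ID ranges reserved for a site or a limit on enrolment at a site.

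**The concern.** The two sections do not fit together. Section 3 states a fixed split within each site. Section 6 controls the ratio only over the list as a whole. When two sites take the next number from a common sequence, the numbers that fall to Lima are in effect a random subset of the list, and nothing forces half of them to be imiquimod.

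Two things are at stake. The first is the by-site comparison, which has only about 20 patients per treatment at each site even if all goes to plan. The second is the crude comparison of arms. Section 15 plans chi-square tests and Kaplan-Meier curves and does not describe either as stratified by site. If cure rates differ between the sites, a chance imbalance of site between arms shifts those crude results. Allocation cannot be repaired once patients are enrolled.

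**Working it through.** **Inputs.** Total 80 and 40 per site, split 20 + 20 (Section 3). One list of 80 at 1:1, issued in sequence to both sites (Section 6). 40 per arm, hazard ratio 2.6, cure 35% versus 67%, power 80% (Section 15). Two-sided 5% significance is assumed, because the protocol does not state it.

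**1. The plan's own power figure.** Freedman's formula with hazard ratio 2.6 needs (1.96 + 0.84)² × (3.6/1.6)² ≈ 40 events. Expected events are 40 × (0.35 + 0.67) = 40.8. Power is Φ(√40.8 × 1.6/3.6 − 1.96) = Φ(0.88) = 81%. The stated 80% is reproduced. Site does not enter this calculation, so the site split does not change it.

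**2. Split within a site.** Assume that the list holds exactly 40 imiquimod and 40 placebo, and that each site enrols 40. The number k of imiquimod patients at Lima is hypergeometric:

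P(k) = C(40, k) × C(40, 40 − k) / C(80, 40)

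P(20) = (1.378 × 10¹¹)² / (1.075 × 10²³) = 0.177

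With arm totals fixed, 20:20 at Lima implies 20:20 at Cusco, so 17.7% is the probability for both sites together. The standard deviation of k is √(40 × 0.5 × 0.5 × 40/79) = 2.25.

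| Split at a site | Probability |
|---|---|
| exactly 20:20 | 17.7% |
| anything else | 82.3% |
| 18:22 or worse | 50.3% |
| 17:23 or worse | 26.3% |
| 15:25 or worse | 4.4% |

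**3. Blocks on the common list.** Permuted blocks of 2, 4, 8, 10 or 20 on the single list, with the two sites' enrolments randomly interleaved (20,000 simulated lists per block size), give 20:20 with probability 17.1% to 17.8%. Blocking without site strata does not help when the sites recruit together.

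**4. Information within a site.** Relative to 20:20, a split a:(40 − a) keeps a(40 − a)/400 of the information: 17 × 23/400 = 97.8%, and 15 × 25/400 = 93.8%.

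**5. Shift in the crude arm difference.** With 17:23 at Lima and the mirror image at Cusco, Lima patients form 17/40 = 42.5% of one arm and 23/40 = 57.5% of the other, a gap of 15 points. With 15:25 the gap is 62.5% − 37.5% = 25 points. The shift is this gap times the difference in cure between sites. The protocol does not give that difference, so a range of 10 to 30 points is assumed. The shift is then 1.5 to 4.5 points for 17:23 and 2.5 to 7.5 points for 15:25, against a design effect of 67% − 35% = 32 points.

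**The case against.** The best defence is that Section 6 does not exclude a list built in site-specific ranges, say 1-40 and 41-80, and that such detail may sit in a randomisation specification not shown. That is possible. But the text says that numbers go out in sequence at enrolment and describes one supply route for both sites, which reads most naturally as one common sequence. The mismatch lies between two sections of the protocol itself, so the protocol has to settle it.

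The second defence is that the harm is limited, and much of this stands. Randomisation remains valid. Section 15 foresees small-sample imbalances and plans Cox models adjusted for baseline characteristics. It lists region of residence among the characteristics to be described, and Section 5 verifies species by PCR. Site and species are not named as covariates, however, and the chi-square and Kaplan-Meier comparisons are not described as adjusted.

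A reader might infer more than the documents support:

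- That the single list *cannot* give 20 + 20. It can, by chance, about 18% of the time.
- That species is a strong prognostic factor here. The protocol gives no cure rates by species, and Section 1 reports increased cure in both.
- That a site imbalance is exactly a species imbalance. Section 3 says only that one species predominates at each place.
- That the species comparison is a formal objective. Section 2 concerns the whole population, and Section 15 powers no comparison by species.
- That even the overall 1:1 is loose. Section 15 plans 40 per group, which points to a list with fixed 40:40 totals.

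**Conclusion.** The point holds as an inconsistency between Sections 3 and 6, with a moderate consequence. Followed as written, the allocation procedure misses the stated split about 82% of the time and gives 17:23 or worse about one time in four. Section 3 sets a target of 40 per site, but no enrolment rule holds either site to it.

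Overall balance and power are untouched, and the loss of information within a site is small (2% at 17:23, 6% at 15:25). What remains is an avoidable chance imbalance of site between arms. It affects the by-site comparison and the unadjusted analyses, and the Cox adjustment can correct it only in part.

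The probabilities rest on three assumptions: fixed 40:40 list totals, 40 patients per site, and one common sequence. If the common list were in small blocks and one site filled its 40 places before the other began, the split would come out even, but nothing in the protocol plans recruitment that way.

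**What to change.** Amend Section 6 so that randomisation is stratified by site. One way is two lists from the same statistician, Lima IDs 1-40 and Cusco IDs 41-80, each with 20 imiquimod and 20 placebo, each drawn in sequence for its own site, with a stated cap of 40 per site. The route through coordinator and pharmacist can stay. The split is then 20 + 20 with certainty once a site has enrolled 40, and the total, the arm sizes and the power calculation do not change.

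If the sponsor prefers a single common list, remove the fixed 20 + 20 statement from Section 3. That makes the protocol consistent but leaves the exposure to site imbalance.

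The cost of stratifying is to regenerate the list and relabel the packages, which must be done before first enrolment. The real downside is less flexibility: with a cap of 40, one site cannot make up the other's recruitment shortfall unless the cap is relaxed.

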## **7. Treatment**

The randomized treatment assignment will take place on Day 1. In the case of bacterial superinfection, patients will receive a complete course of oral or systemic antibiotic treatment (i.e., dicloxacillyn or clindamycin) to clear the infection before entry into the trial (during the screening period).

The nurse will record the drug administration of each patient in the CRF and the doctor will record adverse effects and clinical outcomes in the CFR.

**7.1 Antimonial treatment:**

The total dose of pentavalent antimony (20 mg Glucantime™ /kg body weight/per day) for 20 consecutive days will be administered by intravenous with a syringe gauge # 23. Injections will be given by the nurse in alternating sites (i.e. veins in upper arms). Because a total of 20 injections will be administered during the course of the study, care must be taken to ensure that injections are not administered in the same exact location.

**7.2 Imiquimod and placebo treatment:**

On Day 1 of treatment, the treatment package containing the assigned therapy for an individual patient will be opened and the sachet containing imiquimod or placebo cream will be applied to the cutaneous lesion. Wearing gloves, the nurse will clean the lesion using saline solution removing debris or scab. The nurse will apply the cream on the entire area of each lesion (including a 0.5 cm margin of normal skin). The cream will be applied in the morning and will be rubbed into the lesion(s) until no longer visible. Each sachet will contain approximately 250 mg of cream and the lesion will receive between 125–250 mg of cream. The topical treatment will be applied three times per week (p.e. Monday, Wednesday, Friday or Tuesday, Thursday and Saturday) , in total 9 applications concurrent with the 20 day course of treatment with pentavalent antimony. Only new unopened sachets provided by 3M pharmaceuticals will be used for each treatment.

The lesion will remain uncovered for at least 30 minutes following application during which time the study doctor will record all symptoms of the patient. It will not be necessary to use occlusive dressings for lesions on the face. However, for the lesions not on the face, the lesion(s) will be covered to prevent cream removal by clothing. The patients will be instructed to remove the cover and wash the lesions approximately 8 h following treatment and each following morning.

After each treatment, the study doctor will evaluate the patient for 30 minutes. In the event of an acute reaction, appropriate medical care will be provided by the

physician as appropriate. After the 30-minute observation period, the patient can continue to do his/her daily activities and return to the clinic on the following day.

## 8. Evaluation of Clinical Response

The clinical response will be evaluated using standard descriptive criteria for assessing the size and severity of the cutaneous lesion. This will include, but will not be limited to: size of lesion, reduced ulceration, re-epithelialization, and inflammation reduction. The evaluation will be recorded by the study doctor and recorded on the **clinical report form (CRF)**.

### 8.1 Criteria to evaluate the response to treatment (efficacy)

A standard scale will be used:

| Stage | Observations                                                                                                                                |
|-------|---------------------------------------------------------------------------------------------------------------------------------------------|
| M0    | No improvement. The lesion is active and has the same characteristics or has become larger than before the start of treatment.              |
| M1    | The size of the lesion is decreased ~50% in comparison with the initial lesion. Less inflammatory signs with discrete re-epithelialization. |
| M2    | The size of the lesion is decreased between 50-90% in comparison with the initial lesion. Few inflammatory signs, less than M1.             |
| M3    | The size of the lesion is decreased more than 90% with re-epithelialization and very little inflammation.                                   |

|    |                                                                               |
|----|-------------------------------------------------------------------------------|
| M4 | Complete re-epithelialization with a characteristic scar and no inflammation. |
|----|-------------------------------------------------------------------------------|

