#### **8.7 Analysis of the response to therapy at 1, 2, 3, 6, 9, 12 months of follow-up:**

Improvement: Significant reduction in the size of the lesion at the time of evaluation (Stages M1-M3) compared to baseline.

Cure: Complete re-epithelialization of the lesion without inflammation (Stage M4).

Failure: Any one of the following or combined options

Stage MO at 1 month of follow up after the treatment

Stage M1 at 3 months of follow up after the treatment

Regression of the clinical stage to a lower stage or development of a new lesion.

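### The M scale has a gap below M1 and an overlap between M1 and M2, and M1 at month 3 counts as both Improvement and Failure; those two classes are ill-defined, though cure is not affected

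*Protocol*

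**What the plan says.** Section 8.1 of the protocol defines five stages. The ones that matter here are:

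- The lowest stage, M0, is worded as "The lesion is active and has the same characteristics or has become larger than before the start of treatment".
- The next stage up, M1, is worded as "The size of the lesion is decreased ~50% in comparison with the initial lesion", and its added descriptor is "Less inflammatory signs with discrete re-epithelialization".
- The stage above that, M2, is worded as "The size of the lesion is decreased between 50-90% in comparison with the initial lesion", and its added descriptor is "Few inflammatory signs, less than M1".

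M3 is a reduction above 90%, and M4 is full re-epithelialization without inflammation.

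Section 8.7 turns the stages into response categories at months 1, 2, 3, 6, 9 and 12. Cure is M4. The middle category reads "Improvement: Significant reduction in the size of the lesion at the time of evaluation (Stages M1-M3) compared to baseline". Failure is met by any of three options. Two are tied to a visit: the earlier one is "Stage MO at 1 month of follow up after the treatment" and the later one is "Stage M1 at 3 months of follow up after the treatment". The third is a fall to a lower stage or a new lesion.

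Under section 9.1 a patient with several lesions takes the stage of the least improved one.

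**The concern.** A response scale that feeds named categories should give every lesion one stage, and every patient one category, at each visit. Here neither holds, and the faults lie where the dated failure rules decide. The month 1 rule separates M0 from M1, where there is a gap. The month 3 rule separates M1 from M2, where there is an overlap. At month 3 an M1 patient also sits in two categories at once.

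At stake is the meaning of any reported Improvement or Failure proportion. Stages are scored by study doctors at the visit and entered on the CRF (sections 8 and 9.1), at two sites. A later analysis plan can say which category prevails. It cannot rebuild stages that different doctors assigned using different private cut-offs.

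**Working it through.** **The plan's own figure, to see whether it depends on these stages.** Section 15 states 80% power with 40 per arm, cure of 35% against 67%, and a hazard ratio of 2.6. It gives no significance level; I assume 0.05 two-sided.

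- Hazard ratio: ln(1 − 0.67) / ln(1 − 0.35) = 2.574, which rounds to the stated 2.6.
- Expected cures: 40 × (0.35 + 0.67) = 40.8.
- Freedman log-rank: √40.8 × (2.574 − 1)/(2.574 + 1) − 1.96 = 2.81 − 1.96 = 0.85, so power is 80.3%.

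The stated figure is reproduced. Every input is a cure proportion, so M0 to M3 do not enter.

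**Gap and overlap.** I assigned each whole-percent reduction to a stage as section 8.1 is written: M0 for 0% or less, M1 for 50 ± T, M2 for 50 to 90, M3 above 90. T is my assumption, because the protocol gives no tolerance for its approximate 50%.

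| T (points) | Reductions with no stage | Reductions that are both M1 and M2 |
|---|---|---|
| 0 | 1–49% (49 values) | 50% |
| 5 | 1–44% (44 values) | 50–55% |
| 10 | 1–39% (39 values) | 50–60% |
| 20 | 1–29% (29 values) | 50–70% |

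A wider tolerance narrows the gap but widens the overlap. None of these readings removes either fault. The inflammation descriptors are relative (less, few, less than M1), so they do not settle the boundary.

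**Effect on the failure rules.**

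- Month 1, lesion 20% smaller: at every T above this is neither M0 nor M1. A doctor who rounds down records Failure; one who rounds up records Improvement.
- Month 3, lesion 50% smaller: scored M1 it meets Failure and also Improvement; scored M2 it meets Improvement only.
- Regression: an unchanged lesion near 50%, scored M2 at one visit and M1 at the next, becomes a Failure although nothing has happened to it.

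**Double listing.** Section 8.7 puts M1 under Improvement at any evaluation and puts M1 at month 3 under Failure. It states no order of precedence.

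**Missed visits.** M0 at month 3 after a missed month 1 meets neither dated rule. The regression option catches it if a higher stage was recorded in between. If not, M0 at month 3 is in no category, since Improvement begins at M1. Likewise, M1 first recorded after a missed month 3 is caught only if an earlier stage was higher.

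**Size measure.** The text does not say whether size is area or diameter. With constant shape, a 30% fall in diameter is a 1 − 0.7² = 51% fall in area, and a 50% fall in diameter is a 1 − 0.5² = 75% fall in area. The choice alone can change the stage.

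**The case against.** The strongest reply is that the planned efficacy analysis does not use these stages. Section 3 makes clinical cure the endpoint. Section 15 compares proportions cured and time to cure, and specifies no comparison of failure proportions. That stands, and it limits the importance of the point. A reader might infer that the trial's main result is compromised; the documents do not support that.

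A reader might also infer that the loose boundaries let an unblinded assessor favour one arm. The protocol does not support that either. Section 6 keeps the nurse, doctor and technician blinded through treatment and evaluation, and section 14 describes a placebo identical in appearance. Under blinding, the ambiguity mainly adds noise common to both arms.

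A third tempting step is to put a size on the effect. Supposing that 10 to 25% of the 80 patients (8 to 20) have a small reduction at month 1 yields a shift of 10 to 25 points in the failure proportion. That only restates the supposition. It also requires all such patients to be scored the same way, and it says nothing about a difference between arms.

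Finally, a sensible doctor might put a 20% reduction in M1, and a specific failure rule may naturally override a general description of improvement. Both readings are plausible, but the protocol states neither. Precedence and missed-visit handling could be left to an analysis plan; the stage boundaries could not, because they are applied at the bedside. The missed-visit cases are also narrower than they look, because the regression option catches many of them.

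**Conclusion.** The point holds for the Improvement and Failure classes only. As written, the M scale is neither exhaustive nor exclusive. The two dated failure rules turn on its faulty boundaries, the regression rule inherits the M1/M2 overlap, and M1 at month 3 belongs to two categories.

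The gap spans 29 to 49 whole-percent values for tolerances from ±20 points down to none, and that tolerance is my assumption. The number of patients affected, and any difference between arms, cannot be derived from the protocol. Cure, time to cure and the 80% power are untouched. It should be corrected because the rules conflict on their face, the repair is cheap before enrolment, and stages scored under undefined cut-offs may not be recoverable later.

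**What to change.** Before enrolment:

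1. Reword section 8.1 and the CRF stage labels so that the stages are contiguous, non-overlapping bands covering every possible change in size. The investigators should set the cut-offs.
2. State one size measure, area or diameter, and use one already recorded at follow-up. Section 9.1 has lesion size noted at each follow-up visit. Lesion tracings are listed only for Day 1 (8.2.6) and Day 10 (8.4.6), so a scale tied to follow-up tracings would add a procedure.
3. Reconcile section 8.7 so that each patient falls in one category at each visit, for example by restricting Improvement to patients who do not meet Failure.
4. Have the investigators say how M0 or M1 first recorded after a missed dated visit is classed.

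The cost is minor rewording and new CRF labels, with no new visits. The one drawback is a possible small departure from what section 8.1 calls a standard scale, which could matter for comparison with earlier trials.
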